### Measurement of outcomes

2.5

Vascular anatomy and preoperative design results of the anterolateral thigh flap will be recorded, and intraoperative and preoperative comparisons will be analyzed to explore the clinical efficacy of postoperative patients. After the completion of image digitization, 2 physicians who have been working on the anterolateral thigh flap for more than 4 years read the images in a double-blind way to evaluate whether the location, shape, and scope of the lesion of the patient has invasion or metastasis. When opinions will be different, they read the images together and agreed. Consistency analysis by CTA joint digital technology, digital technology and CTA in the defects of head and neck cancer patients in the orientation of value, when the CTA inspection found perforators preoperative and intraoperative confirmed existence is judged to be (+), when the digital technology can be worn for successful reconstruction is judged to be (+), either in the joint inspection tests to determine the (+), finally to the 3 ways to wear the positioning performance comparison.

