### Study method

2.2

1.The patients will complete routine preoperative examination to exclude serious systemic diseases, and received enhanced valvular CT scan, so that the doctor could determine the lesion scope and vascular condition in the recipient area;2.The patients will be placed in the supine position, the middle and upper 1/3 of both lower extremities will be radiographically marked, and both lower extremities will be kept naturally straight. Iohexol injection will be injected intravenously from the middle of the elbow. A 256-slice spiral CT (Philips, USA) will be used for continuous CTA scanning from bilateral anterior superior iliac spine to bilateral lower edge of patella. CT scanning parameters will be set as 0.625 mm thickness, 120-140 kV, and 525 mA.3.CTA data preprocessing, search for puncture and define reconstruction area: obtain CTA data in DICOM format and import CTA data into 3-D15.0 software (Materialize, Belgium). After reading the data, 3-D15.0 software automatically creates a 3-D project file and uses the convert function to complete the data conversion and generate the original CTA image. Based on the original cross section, the software automatically reconstructs the continuous sectional images of sagittal plane and coronal plane to form the observation screen of 3 dimensions. The original CTA images will be scanned and observed in three orthogonal sectional views to determine the appropriate location of the perforation of the anterolateral femoral flap. Then, the 3-D reconstruction area will be restricted to 1 side of the supply area with suitable cutting struts with Crop Mask, thus reducing the workload of data segmentation in later period.4.3-D is used to reconstruct bones, blood vessels and skin: a section line is created by using the section line option in the axial window, and the gray value distribution along the line can be obtained. To better observe the transition of soft tissue, cortical bone and cancellous bone, click the option of Start Thresholding and select a certain amount of pixel gray value to segment the bone from anterior superior iliac spine to ipilateral patella. The soft tissue and some discrete voxels are then separated from the bone by means of regional growth. Select the region growth tool from the segmentation toolbar and click on the bone section to add all associated voxels to the new mask. The hip, femur, and patella will be extracted from the shape and outline of the bone at each axis view level using a multi-layer editing tool. The newly added mask will be reconstructed in 3-D to extract the individual bone model. Adjust appropriate thresholds to create a new mask, use a multi-layer editing tool on the axis view to erase irrelevant grayscale values, and retain and extract major blood vessels and perforations. The erased new mask will be reconstructed in 3-D, and the reconstructed plane mask will be duplicated. Use the Edit Mask in 3-D to edit the reconstructed 3-D model. Remove the irrelevant soft tissue with the cover lock tool. Click the erase tool to remove the selected pixels from the Mask. After the 3-D editing function is completed, close the toolbar and carry out 3-D reconstruction on the edited corresponding plane mask, so as to obtain clear blood vessels and perforating branches. Reconstruct the thigh skin, create a new mask, set the segmentation threshold, erase the gray value of irrelevant structure on the axis view, carry out 3-D reconstruction, and use the wrap function to make the reconstructed skin continuously smooth.5.3-D visualization of the model: give bone and blood vessel an opaque and skin transparency High, which allows observation and determination of bone and blood vessel through the skin. To enhance the visual effect, the target perforations and pedicles can be stained to a specific color. Based on the size and shape of the wound in the receiving area and the cutting function in the simulation option, the scope, depth and path of the flap will be simulated along the skin surface to generate a 3-D visual model of the personalized free anterolateral thigh flap.6.Simulated skin flap removal and operation: 3-D will be used to edit and process the reconstructed 3-D model before surgery. After other parts will be hidden, the designed anterolateral thigh flap will be “removed” from the 3-D model together with the vascular pedicle. The simulated data will be transferred to the intraoperative body surface of the patients, and the flap will be surgically removed to verify the accuracy of perforator location, and the anterolateral thigh flap will be transplanted and repaired for head and neck soft tissue defects.7.Routine nursing care after free flap transplantation will be given to promote wound healing. Preoperative and intraoperative measurement data will be processed and analyzed with SPSS20.0 software.

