### Statistical analysis

2.6

Statistical analyses will be implemented by SPSS 17.0 and Microsoft Excel 2007 software. Data will be represented as mean ± standard deviation (SD). A *t*-test will be performed to compare the changes in measures within groups. Statistical significance will be considered at *P* < .05.

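### The only test fixed is a within-group t-test; if applied to preoperative versus intraoperative measurements, it tests mean error and cannot show localisation accuracy or agreement

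*Protocol article*

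**What the plan says.** Section 2.5 (Measurement of outcomes) begins with the planned data: "Vascular anatomy and preoperative design results of the anterolateral thigh flap will be recorded". It continues that "intraoperative and preoperative comparisons will be analyzed to explore the clinical efficacy of postoperative patients".

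Section 2.2 (Study method) gives the purpose. The simulated design is transferred to the patient's body surface, and "the flap will be surgically removed to verify the accuracy of perforator location". The section closes with "Preoperative and intraoperative measurement data will be processed and analyzed with SPSS20.0 software". Section 2.4 (Interventions) adds that the preoperative indicators are measured again during surgery, in three groups of 20.

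Section 2.6 (Statistical analysis) names one inferential procedure, a t-test that "will be performed to compare the changes in measures within groups", at P < .05, with data summarised as mean ± SD. It gives no limits of agreement, intraclass or concordance correlation, absolute localisation error or equivalence margin.

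Section 2.5 also announces a consistency analysis. It is tied to positive calls by CTA, digital technology and the joint test, and names no statistic.

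**The concern.** The purpose is accuracy: how far the preoperative plan lies from what the surgeon finds, patient by patient. A paired t-test addresses something else, namely whether the errors average to zero. A method that misses widely in both directions can have a mean error near zero. Greater scatter also enlarges the standard error, so a real systematic error becomes harder to detect. A non-significant result therefore says little about agreement, and a significant one may reflect a small and very consistent offset.

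At stake is the interpretation of the measured preoperative and intraoperative data, which are the trial's direct evidence on whether the digital plan carries over to the patient.

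**Working it through.** **Is there a figure to reproduce?** No. The article gives 20 per group without a derivation, and no SD, bias, tolerance or agreement margin. The millimetre values below are assumptions shown over a range. The significance results depend only on the ratio of bias to SD.

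**Inputs**
- n = 20 per group (section 2.4), assuming one complete pair per patient.
- Alpha 0.05 (section 2.6). Sidedness is not stated; two-sided is assumed.
- Within-group t-test (section 2.6), taken as paired, with normally distributed differences.

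**Step 1. Threshold for significance.** The statistic is t = mean error / (SD/√n). With 19 degrees of freedom the critical value is 2.093, so P > .05 whenever

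|mean error| < 2.093/√20 × SD = 2.093/4.472 × SD = 0.468 SD.

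The threshold grows in proportion to the scatter.

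**Step 2. Two single results.** Limits of agreement are bias ± 1.96 SD.
- Observed mean error 2 mm, SD 10 mm: t = 2/(10/4.472) = 0.894, P = 0.38. Limits: 2 ± 19.6 = -17.6 to 21.6 mm.
- Observed mean error 1 mm, SD 1 mm: t = 1/(1/4.472) = 4.472, P = 0.0003. Limits: 1 ± 1.96 = -1.0 to 3.0 mm.

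These examples change bias and SD together, so Step 3 holds the bias fixed.

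**Step 3. Chance of a non-significant result at a fixed true bias.** This comes from the noncentral t distribution with 19 degrees of freedom and noncentrality bias/SD × √20. The share of patients within 5 mm (an assumed tolerance) is from the normal distribution.

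| True bias (mm) | SD (mm) | P > .05 | 95% limits (mm) | Within 5 mm |
|---|---|---|---|---|
| 2 | 2 | 1.1% | -1.9 to 5.9 | 93.3% |
| 2 | 3 | 19.3% | -3.9 to 7.9 | 83.2% |
| 2 | 5 | 60.3% | -7.8 to 11.8 | 64.5% |
| 2 | 10 | 86.4% | -17.6 to 21.6 | 37.6% |
| 2 | 20 | 92.9% | -37.2 to 41.2 | 19.6% |
| 5 | 5 | 1.1% | -4.8 to 14.8 | 47.7% |
| 5 | 10 | 43.5% | -14.6 to 24.6 | 34.1% |
| 5 | 20 | 81.4% | -34.2 to 44.2 | 19.1% |
| 0 | 2 | 95% | -3.9 to 3.9 | 98.8% |
| 0 | 20 | 95% | -39.2 to 39.2 | 19.7% |

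Simulation with 200,000 samples agrees: power is 0.989 at bias 2, SD 2 and 0.136 at bias 2, SD 10.

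At a given non-zero bias, the chance of a non-significant result rises as precision falls. At zero bias it is 95% at every SD, so the test does not distinguish a good locator from a poor one.

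**Step 4. What the alternative can deliver at n = 20.** The 95% confidence interval for each limit has half-width

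2.093 × √(1/20 + 1.96²/(2 × 19)) × SD = 2.093 × √(0.0500 + 0.1011) × SD = 0.81 SD.

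At SD 5 mm that is about ±4.1 mm (0.81 × 5). The limits order the methods correctly by scatter, but imprecisely.

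**The case against.** **The link to the t-test is an inference.** Section 2.5 names no test for this comparison, section 2.2 names only software, and section 2.6 mentions neither pairing nor the preoperative/intraoperative contrast. This is correct and should be said openly. The inference is still the only reasonable one, because the article describes no other test and no other repeated measurement within a patient.

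**No decision rule is stated.** A reader might infer that the trial will declare a poor locator consistent with surgery and a precise one inconsistent. The article never says that P > .05 will be read as agreement, and section 2.5 describes the aim of the comparison as exploring efficacy. The reversal is therefore conditional. The mismatch does not depend on that reading: if a significant result counted as success, the test would favour systematic mislocation.

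**The test does not always favour imprecision.** A reader might generalise that it rewards the noisier method. That needs a non-zero bias; with zero bias it rewards neither.

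**Positioning is also judged another way.** The article names flap survival rate, sensitivity, specificity and accuracy as outcomes, and section 2.5 ends with a comparison of the three ways based on positive calls. A reader might infer that the trial's whole conclusion on positioning hangs on the t-test; the documents do not support that. Equally, the binary comparison does not cover measured quantities and so does not repair their analysis.

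**It is a condensed article and the SAP is not shown.** An agreement statistic could be left to the SAP. But the point here is not an omission: the article fixes a test that does not match the purpose it gives, and an SAP that follows it would inherit the mismatch.

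**Conclusion.** The point holds in conditional form. If the within-group t-test is the analysis of preoperative against intraoperative measurements, as the article implies, it is the wrong tool for verifying localisation accuracy. It examines only the mean error, and with 20 patients it is silent on any observed mean error below 0.47 SD.

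If, in addition, non-significance is read as agreement, then at an assumed 2 mm bias a method with SD 10 mm passes about 86% of the time and one with SD 2 mm about 1%. The millimetre values are illustrative, and the calculation assumes a two-sided paired test, normal differences and 20 complete pairs. It is worth correcting, because the affected data bear on a stated purpose of the study and the change is small.

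**What to change.** In section 2.6, for each quantity measured both before and during surgery, replace the within-group t-test by the mean difference (bias) with 95% limits of agreement and confidence intervals for the bias and for each limit, separately for the three groups. State that a non-significant difference will not be taken as evidence of agreement.

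Where planned and found perforator positions are recorded at the verification step, also summarise the absolute distance between them per patient and compare it across the three groups. Keep the binary positive-call comparison as a separate analysis.

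**Cost.** The first change is wording only and uses measurements already planned. The second may need a small addition to data capture, because the article does not list planned and found positions, or the distance between them, as recorded items. With 20 patients each limit is uncertain by about ±0.8 SD, so the intervals will be wide and should be reported as such. No extra patients are needed.

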### Interventions

2.4

Patients will be randomly divided into CTA group (n = 20), mimics group (n = 20) and CTA + mimics group (n = 20) according to the numerical table. Patients in the CTA group will receive CTA examination of lower extremities. Patients in mimics group will receive digital technology in the positioning of perforator. Patients in CTA + mimics group will receive CTA + digital technology. All the patients will receive the flap cutting and the flap making; the doctor will determine the perforation branch of the flap with 3-D visual positioning, measure the preoperative indicators intraoperatively and complete the wound repair. Finally, the survival rate, sensitivity, specificity and accuracy of the flap will be measured.

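### The only double-blind two-reader assessment is aimed at the tumour lesion, so no blinded reading is specified for the thigh perforator call behind sensitivity, specificity and accuracy

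*Protocol article*

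**What the plan says.** Section 2.5 (Measurement of outcomes) describes one blinded assessment. It states that "2 physicians who have been working on the anterolateral thigh flap for more than 4 years read the images in a double-blind way", and that the purpose is "to evaluate whether the location, shape, and scope of the lesion of the patient has invasion or metastasis". Disagreements go to consensus: "When opinions will be different, they read the images together and agreed".

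The same section then defines positivity for perforator location:

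- CTA: "when the CTA inspection found perforators preoperative and intraoperative confirmed existence is judged to be" (+).
- Digital technology: "when the digital technology can be worn for successful reconstruction is judged to be" (+).
- Joint test: (+) if either component is (+).

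It closes with the comparison the trial is for: "finally to the 3 ways to wear the positioning performance comparison". None of these rules names a reader, a blinding condition or a consensus step. Section 2.4 (Interventions) says that "the doctor will determine the perforation branch of the flap with 3-D visual positioning", without mentioning blinding. The Abstract and sections 2.1 and 2.4 give the same four outcomes: survival rate, sensitivity, specificity and accuracy.

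**The concern.** Sensitivity, specificity and accuracy depend on a subjective image call: is there a perforator, and where? Blinded independent reading with a consensus rule is the usual protection for such a call. The article provides that protection but attaches it to a different question, namely the extent and spread of the tumour. A reading form built from this sentence would collect blinded lesion scores and no blinded perforator scores. The diagnostic comparison between arms would then rest on calls whose independence from the operative finding the protocol does not secure.

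This is not a detail left out by a condensed article. The reading procedure is described, and its stated target does not match the outcomes.

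**Working it through.** The plan gives no figure on this point, so the check compares passages and adds a short piece of algebra for the CTA rule.

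**1. Does the lesion reading feed an outcome?** Of the four stated outcomes, one is flap survival and three are diagnostic measures of perforator positioning. Lesion invasion or metastasis enters 0 of 4.

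**2. Can the lesion be seen on the digitized images?** Section 2.5 places the reading after image digitization. In section 2.2 (Study method) the data that are digitized are the lower-limb CTA, from the iliac spine to the patella, and they are viewed "to determine the appropriate location of the perforation of the anterolateral femoral flap". The patients have laryngeal cancer (section 2.3). Lesion scope is judged on a separate enhanced CT in item 1 of section 2.2. The thigh images therefore cannot answer the question put to the readers.

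**3. Is a blinded perforator reading specified elsewhere?** No. The three (+) rules in section 2.5 and the positioning step in section 2.4 state no blinding.

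**4. What does the CTA rule do to the counts?** Cross-classify CTA finding by operative finding:

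| | Present at surgery | Not confirmed at surgery |
|---|---|---|
| Found on CTA | a | b |
| Not found on CTA | c | d |

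With N = a + b + c + d, and (+) defined by the preoperative reading alone:

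- sensitivity = a/(a + c)
- specificity = d/(b + d)
- accuracy = (a + d)/N

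Under the rule as written, only cell a is (+). If the b findings are then counted as (−), they become true negatives:

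- sensitivity = a/(a + c), unchanged by the recoding
- specificity = (b + d)/(b + d) = 1
- accuracy = (a + b + d)/N, higher by b/N

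False positives are thus removed by definition. The article gives no value or expected rate for b, so b/N cannot be filled in.

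**5. Does the same hold for the digital method?** Its (+) is a successful reconstruction, with no operative element. Item 6 of section 2.2 puts model editing and simulated flap removal before surgery and uses the operation to verify the location afterwards. The algebra in step 4 does not apply to it. The joint test takes in the CTA rule only through its CTA component.

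**The case against.** The strongest reply is that this is a drafting slip. The readers are thigh-flap physicians, they read after digitization, and the digitized data are thigh images. All of this suggests that a perforator reading was meant and that the target phrase is garbled, in an article with other visible language errors. That is plausible, and it limits how much can be concluded about what the investigators will do. It does not rescue the sentence, which names the wrong target and needs correcting either way.

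Three stronger readings are tempting, and the documents do not support them.

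- **That the perforator call is established as unblinded.** The (+) rules name no reader. Silence is not evidence of an unblinded call, and the full protocol may assign readers.
- **That accuracy is inflated for every method.** Only the CTA rule contains the operative result. The digital reconstruction is completed before surgery, so any bias there would have to come from unblinded judgement, which is a possibility and not something the text shows.
- **That the lesion reading is worthless.** Section 2.2 bases flap design on the size and shape of the recipient wound, and section 2.5 records preoperative design results. Lesion assessment may inform those, although it does not enter the diagnostic outcomes.

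It is also fair to say that the CTA rule is a separate defect: correcting the readers' target would leave it in place. The fix therefore has to deal with it explicitly.

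**Conclusion.** The point holds in this form: the only double-blind consensus reading in the article is directed at a target outside all four stated outcomes and outside the field of the digitized CTA. No blinded reading is specified for the perforator call behind three of those outcomes. For CTA, the call cannot be blind to the operative reference, because operative confirmation is part of its definition.

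The size of any bias cannot be derived. The upward direction is supported for CTA only, for specificity and accuracy through the recoding shown above, and it assumes that CTA findings not confirmed at surgery are counted as (−). The conclusion rests on the published wording. It would be softened if the full protocol states a preoperative, blinded perforator reading. The sponsor should correct this before readings begin.

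**What to change.** In section 2.5:

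- Restate the target: the same two physicians independently record, before surgery, the presence and marked position of the anterolateral thigh perforator on the images available in the patient's allocated arm. In the combined arm, read each method blind to the other where feasible. The single-method arms have no second reading to be blinded from.
- Say what double-blind means here: blind to the other reader and, by timing, to the operative finding.
- Lock the two independent readings, then the consensus, before the operation. The locked pair also gives the announced consistency analysis independent readings to use.
- Define CTA (+) by the preoperative reading alone, and keep intraoperative confirmation as the separate reference standard.
- Take the lesion reading out of the accuracy outcomes. It can stay as part of surgical planning.

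The cost is a few sentences in section 2.5, a reading form and a little reader time, with no extra staff.

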## Abstract

**Background::**

Head and neck tissue defects cause great physical and psychological damage to patients. Therefore, accurate positioning of perforating vessels before operation is of great significance for improving the success rate of flap preparation and avoiding unnecessary incision injury.

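### The (+) rule in section 2.5 scores detection or reconstruction of a perforator, with no location criterion, yet it carries the comparison of positioning between the three methods

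*Protocol article*

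**What the plan says.** The Background of the abstract gives the purpose of the trial: "accurate positioning of perforating vessels before operation is of great significance for improving the success rate of flap preparation". Section 2.4 (Interventions) names the outcomes: "Finally, the survival rate, sensitivity, specificity and accuracy of the flap will be measured".

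Section 2.5 (Measurement of outcomes) holds the only scoring rule in the article. It has three branches:

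- **CTA, then digital technology:** "when the CTA inspection found perforators preoperative and intraoperative confirmed existence is judged to be (+), when the digital technology can be worn for successful reconstruction", the latter also being called (+).
- **Combined:** "either in the joint inspection tests to determine the" (+), so one positive component is enough.

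The same sentence closes by using these calls to compare the positioning performance of the three methods.

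Location does appear elsewhere. In section 2.2, step 6, the simulated plan is carried over to the patient's body surface and "the flap will be surgically removed to verify the accuracy of perforator location". Step 7 of that section, section 2.4 and the opening of section 2.5 all mention preoperative and intraoperative measurements or comparisons. None of these places gives a distance or a unit, or refers to the (+) call.

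**The concern.** The trial asks which method positions perforators best. A score for that question has to get worse when the predicted site is further from the vessel. The stated rule has no term that does this. Two methods that find or reconstruct perforators equally often would score the same, even if one marks the skin much more accurately.

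If sensitivity, specificity and accuracy are calculated from these calls, the trial could report high accuracy figures that describe detection, and readers would take them as evidence on positioning. A difference between arms could also arise from detection or reconstruction rates alone and be read as a difference in positioning.

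**Working it through.** **1. Is there a figure to reproduce?** No. The article states no expected rate, effect size, power or positional tolerance. The only arithmetic is 3 × 20 = 60 patients, which adds up. The check is therefore of the definition, followed by an illustration.

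**2. What each branch of the rule in section 2.5 requires**

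| Method | Preoperative condition | Surgical condition | Location condition |
|---|---|---|---|
| CTA | perforator seen | existence confirmed | none stated |
| Digital | reconstruction succeeds | none stated | none stated |
| Combined | either of the above | only if the CTA branch is the positive one | none stated |

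The digital branch cannot register a location error, because nothing found at surgery enters it. Through the either-positive rule this passes to the combined method.

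**3. Does another section supply the missing link?** Section 2.2, step 6, states an intention to check location at surgery, without a criterion. The preoperative and intraoperative comparison that opens section 2.5 is tied to postoperative clinical efficacy, not to the (+) call. Section 2.6 plans means, SDs and a within-group t-test. That could suit paired measurements, but it does not compare the three methods and does not mention the call.

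**4. How insensitive is the score?** All inputs here are assumptions. Let e be the probability of a positive call under the stated rule, and q the probability that the vessel lies within tolerance, given a positive call.

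- Score under the stated rule: e
- Score with a location condition: e × q

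With e = 0.95 for two methods, q = 0.95 for one and q = 0.60 for the other:

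- Stated rule: 0.95 − 0.95 = 0
- With location: 0.95 × 0.95 − 0.95 × 0.60 = 0.9025 − 0.57 = 0.33

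**5. The same in millimetres.** Assume a circular normal error on the skin with SD s per axis. Then P(error < d) = 1 − exp(−d²/(2s²)).

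- d = 10, s = 5: 1 − exp(−2) = 0.865
- d = 10, s = 10: 1 − exp(−0.5) = 0.393
- d = 20, s = 5: 1 − exp(−8) = 0.9997
- d = 20, s = 10: 1 − exp(−2) = 0.865

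The gap between the methods is 0.865 − 0.393 = 0.47 at 10 mm and 0.9997 − 0.865 = 0.135 at 20 mm. With equal detection, the stated score shows a gap of 0 in both cases.

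**6. The either-positive rule.** If the components were independent with positive rates of 0.80 each, the combined rate would be 1 − 0.20 × 0.20 = 0.96. With 0.90 each it would be 1 − 0.10 × 0.10 = 0.99. The combined score rises with no gain in location.

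**The case against.** The best defence has four parts.

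**The CTA rule is stricter than bare existence.** It needs detection before surgery and confirmation at surgery, and the natural reading is that surgery confirms the vessel that CTA showed. This stands in part. A reader might infer that the rule scores CTA positive whenever any perforator exists, even one several centimetres from the mark. The text does not say that, and it does not exclude it either. The word used is existence, so two sites could apply it differently. The defence does not reach the digital branch.

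**Location is measured elsewhere.** This is true of the stated intention, so it would be wrong to infer that the trial ignores location. But no measurement is connected to the score that carries the comparison. A condensed article may leave a tolerance in millimetres to the full protocol. Here, however, the article states the rule itself, and states it without any location condition.

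**The link to sensitivity, specificity and accuracy is not written down.** This stands. The link is an inference from the listing of these outcomes and from the use made of the calls; the article gives no other basis for them. The sentence in section 2.5 is also poorly worded, which limits how far its literal text can be pressed.

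**Detection is a legitimate target.** It is, and the rule can separate methods that detect differently. Such a difference would concern detection, while the sentence presents the comparison as one of positioning.

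A separate difficulty remains: section 2.4 gives 3-D visual positioning to all patients, so a location criterion alone would not settle what distinguishes the arms.

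**Conclusion.** The point holds for the scoring rule. As written in section 2.5, the (+) call measures detection (CTA), reconstruction (digital) or either (combined). It does not change with location error, so the positioning comparison built on it does not answer the question set in the Background.

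It is tempting to conclude that every method will score 100% and that the trial loses 47 percentage points of real difference. The documents do not support this. A score of 100% requires complete detection, which is nowhere stated. The 86% versus 39% rests on assumed SDs of 5 and 10 mm, a circular normal error and a 10 mm limit; at 20 mm the gap is 13.5 points. The conclusion that the score ignores location follows from the wording and needs none of these figures. The extension to the reported sensitivity, specificity and accuracy rests on the inference that they come from the (+) calls.

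**What to change.** In section 2.5:

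- Score all three methods against the same intraoperative reference. Count a prediction as correct only if the perforator found at surgery lies within a stated distance of the preoperative mark. The investigators choose that distance and fix it before enrolment.
- Also record perforators found at surgery that were not predicted. If only predictions are scored, missed vessels never enter the denominator and sensitivity cannot be estimated. Sensitivity is then the correctly located perforators divided by all perforators found at surgery.
- Report specificity only if a true negative is defined. Otherwise report positive predictive value: correct predictions divided by all predictions.
- Report the mark-to-vessel distance in mm as the localisation measure, and state that accuracy is calculated from these calls.

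The cost is new wording in section 2.5 and the recording of a distance, and of any unpredicted perforators, within measurements already planned at surgery. Reported accuracy may be lower than under the present rule. The change should be in place before the first operation, because a distance not measured when the flap is raised may not be recoverable later.
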